### Objectives {7}

The specific aims of this study are:Aim 1: To refine the mobile app through focus groups (to vet app content) and usability testing (to optimize app functionality) in English- and Spanish-speaking women. Focus groups will be conducted with women who were employed prior to diagnosis or at the time of consent to the BCW study [7], and who completed (neo)adjuvant chemotherapy for breast cancer. Usability testing will be conducted in individuals who were employed prior to diagnosis and are undergoing or plan to undergo treatment for a diagnosis of cancer.Aim 2: To evaluate the effect of the mobile app on job retention after completion of adjuvant therapy for breast cancer among English- and Spanish-speaking women who were employed prior to diagnosis and plan to undergo chemotherapy.*Hypothesis:* Participants randomized to the app will have higher rates of employment four months, 1 year, and 2 years after treatment completion compared to those randomized to receive the booklet.Subaim 1: To evaluate whether the effect of the app on job retention varies by characteristics including chemotherapy regimen, symptom burden, race/ethnicity, language, and job type.Aim 3: To evaluate the effect of the mobile app on confidence in asking an employer for accommodations and on receipt of workplace accommodations during and following (neo)adjuvant therapy.*Hypothesis:* Participants randomized to the app will have greater improvements in confidence in asking an employer for accommodations and will be more likely to receive requested workplace accommodations compared to those randomized to receive the booklet.Aim 4: To evaluate the effect of the mobile app on patient efficacy in communicating with the oncology provider and self-reported symptom burden during and following adjuvant therapy.*Hypothesis:* Participants randomized to the app will have higher efficacy in communicating with the provider and lower self-reported symptom burden based on the NCI Patient Reported Outcomes Common Terminology Criteria for Adverse Events (PRO-CTCAE®) system compared to those randomized to receive the booklet.Exploratory aim 1: To evaluate the effect of the mobile app on cancer treatment adherence.

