### Outcomes {12}

The primary endpoint of the trial is self-reported employment status 4 months following the completion of treatment. This is the same primary endpoint as was used in the BCW study [7]; timing the assessment of employment status based on the end of treatment rather than the date of diagnosis provides an assessment that is comparable across participants, regardless of the timing between diagnosis and start of treatment. Depending on disease characteristics, provider recommendations, and patient preferences, participants will undergo different chemotherapy regimens with differences in cycle length and total number of cycles. They, therefore, will vary in their overall chemotherapy treatment period. Our endpoint of employment status 4 months following the completion of all treatment, consequently, has a shared interpretation across types of therapy. Two additional assessments will allow us to measure long-term employment status (1 and 2 years after completion of treatment). Patients working full-time or part-time will be considered to be working (job retained) regardless of whether they worked full-time or part-time at baseline.

Secondary study endpoints include change in self-efficacy to ask an employer for accommodations, receipt of workplace accommodations, change in perceived efficacy in patient-physician interactions (PEPPI), and symptom burden. We will ask participants about accommodations requested at baseline and at each on-treatment and post-treatment survey. Those who report asking for accommodations will also be asked to report on whether their request was granted, including whether the request was granted in full, in part, or if they were given a different accommodation instead. Symptom burden will be assessed using relevant items from the Patient-Reported Outcomes version of the Common Terminology Criteria for Adverse Events (PRO-CTCAE®). Details of these analyses are included below. These four secondary outcomes will be evaluated with respect to their relationship with the primary outcome.

The endpoint for the exploratory aim is treatment adherence based on relative dose intensity (RDI), a measure that incorporates both chemotherapy dose-reductions and treatment delays, and for which a standard exists that can be compared across chemotherapy regimens. RDI is expressed as a percent; the commonly accepted threshold below which adjuvant chemotherapy for breast cancer is less effective is 85% [43–45].

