*Sample size for Aim 3:* The percent of participants who express confidence in asking an employer for accommodations will be compared by study arm. This outcome will be evaluated at the mid-point and on the last day of chemotherapy. As a conservative estimate, we expect that 80% of participants will have evaluable data at each of these time-points. Confidence in asking an employer for accommodations based on participant answers to a 5-item scale (see Data collection and management below) will be dichotomized based on the cutoff established in the observational BCW study [7]. Thirty percent of BCW study [7] participants improved their confidence in asking for accommodations between baseline and 4 months post-treatment. In the current study, with a sample size of 167 per arm, we will have 80% power to identify an improvement in confidence of 15% (e.g., 30% of control-arm participants and 45% of those who receive the app) based on a 2-sided test with a 5% type I error.

*Sample size for Aim 4:* Perceived efficacy in patient-physician interactions (PEPPI) at baseline, mid-treatment, and end of chemotherapy treatment will be compared by study arm in 3 *t*-tests. The PEPPI is a 5-item scale (with range 0–50); higher scores indicate greater self-efficacy. In a similar patient sample, the mean was 38 (standard deviation=12). Based on the retention projections described above, we expect to have data for at least *n*=167 per arm at each of the 3 time-points. For each analysis, we will be able to detect a difference from 38 to 42 (>85% power, 2-sided type I error of 5%).

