Aim 3: To evaluate the effect of the TEAMWork App on confidence in asking an employer for accommodations and on receipt of accommodations during and after adjuvant therapy.

*Analysis:* The relationship between the app and confidence asking for accommodations at the mid-point of chemotherapy and 4 months post-treatment will be evaluated using chi-squared tests. In subset analyses, the relationship between job retention and receipt of accommodations will be evaluated among participants who asked for accommodations.

Aim 4: To evaluate the effect of the TEAMWork App on patient efficacy in communicating with the provider and self-reported symptom burden during and following adjuvant therapy.

*Analysis:* Participants randomized to receive the app are hypothesized to have higher efficacy in communicating with the provider and lower symptom burden during and after treatment than those randomized to the informational booklet. Perceived efficacy in patient-physician interactions as measured by the PEPPI score will be compared by arm using the 2-sample *t*-test [22]. For each symptom, we will compare symptom incidence and severity by study arm. To compare symptoms, we will conduct 2 sets of analyses. One will compare the rate of symptom incidence by assigned study arm at the mid- and end-of-chemotherapy-treatment time-points separately. A second analysis will report an arm comparison of whether patients who reported a symptom at the mid-treatment survey experienced an increase, decrease, or cessation of that symptom at the end of chemotherapy treatment. The main analytic tool that will be used for these analyses is the chi-squared test.

Exploratory aim 1: To evaluate the effect of the TEAMWork App on treatment adherence.

*Analysis:* We will compare treatment adherence (RDI) by receipt of the app in a Wilcoxon rank sum test.

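### Aims 3 and 4: PEPPI is tested without its collected baseline score, one of its three tests is at baseline, and the Aim 3 confidence endpoint has conflicting time-points and an unclear definition

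*Protocol article*

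**What the plan says.** Outcomes {12} lists as secondary endpoints "change in self-efficacy to ask an employer for accommodations" and "change in perceived efficacy in patient-physician interactions (PEPPI), and symptom burden". The Aim 3 hypothesis in Objectives {7} is likewise about "greater improvements in confidence in asking an employer for accommodations". The Baseline survey section collects the 5-item PEPPI and combines it with the employer self-efficacy measure taken at eligibility determination, so a baseline value is planned for both scales.

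**PEPPI (Aim 4).** Sample size {14} plans the arm comparison as follows: perceived efficacy ("PEPPI) at baseline, mid-treatment, and end of chemotherapy treatment will be compared by study arm in 3" t-tests. It claims more than 85% power, for each of the three, to detect 38 versus 42. Statistical methods {20a} again names a two-sample t-test on the score, without time-points and without a baseline term.

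**Employer confidence (Aim 3).** Sample size {14} compares the percentage who express confidence, dichotomising the scale at a cutoff from the earlier observational study (BCW). On timing it says: "This outcome will be evaluated at the mid-point and on the last day of chemotherapy". Its planning rate is the 30% of BCW participants who "improved their confidence in asking for accommodations between baseline and 4 months post-treatment". Statistical methods {20a} says instead that "confidence asking for accommodations at the mid-point of chemotherapy and 4 months post-treatment will be evaluated using chi-squared tests".

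**The concern.** There are three separate issues.

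1. Both endpoints are change from baseline and both baselines are collected, but the stated PEPPI test does not use the baseline score. At stake is precision on a secondary aim.
2. One of the three PEPPI comparisons is at baseline. Concealment mechanism {16b} asks participants to complete that survey before they are told their arm. Any arm difference then is chance, so a power claim for an app effect at that time-point has no meaning.
3. The Aim 3 endpoint is not fixed. Its second time-point differs between sections, and both candidates can be carried out, because the scale is collected in the on-treatment and the post-treatment surveys. The text also does not settle whether success means being confident or having become more confident. With no rule between the alternatives, the Aim 3 result could be chosen after the data are seen.

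**Working it through.** **Inputs from Sample size {14}.** PEPPI SD 12, difference 42 − 38 = 4, 167 per arm, two-sided 5%. For Aim 3, 30% versus 45%, 167 per arm.

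**The plan's own figures.**

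- PEPPI: SE = 12 × √(2/167) = 1.313. Power = Φ(4/1.313 − 1.96) = Φ(1.086) = 86.1%, or 85.9% with the noncentral t. The claim of more than 85% reproduces. The difference detectable at 80% power is 2.80 × 1.313 = 3.68 points.
- Aim 3: the pooled rate is 37.5%, the null SE is √(2 × 0.375 × 0.625/167) = 0.0530 and the alternative SE is √((0.21 + 0.2475)/167) = 0.0523. Power = Φ((0.15 − 1.96 × 0.0530)/0.0523) = 81.1%. The stated 80% reproduces. (A continuity correction would give 77.9%.)

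**PEPPI with baseline adjustment.** The protocol gives no baseline-to-follow-up correlation r, so r is assumed over 0.3 to 0.7. The residual SD under ANCOVA is 12 × √(1 − r²). The SD of a simple change score, assuming equal SDs at both times, is 12 × √(2(1 − r)).

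| r (assumed) | ANCOVA SD | ANCOVA power | Detectable at 80% | Change-score power |
|---|---|---|---|---|
| none (as planned) | 12.00 | 86.1% | 3.68 | – |
| 0.3 | 11.45 | 89.1% | 3.51 | 73% |
| 0.5 | 10.39 | 94.0% | 3.19 | 86% |
| 0.7 | 8.57 | 98.9% | 2.63 | 98% |

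Adjustment therefore adds about 3 to 13 points of power. Testing raw change scores is not an equivalent remedy: it has less power than the planned t-test when r is below 0.5 and only equals it at 0.5.

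**Aim 3, sections side by side.**

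| Item | Sample size {14} | Statistical methods {20a} |
|---|---|---|
| First time-point | mid-point of chemotherapy | mid-point of chemotherapy |
| Second time-point | last day of chemotherapy | 4 months post-treatment |
| Test | two-sided 5%, on percentages | chi-squared |

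Within Sample size {14}, the compared quantity is a status (the percentage confident), while the 30% is a rate of improvement from baseline to 4 months post-treatment. The two differ. A woman above the cutoff at baseline and at follow-up is a success on status, but has not newly crossed the cutoff. The protocol gives no control rate for status. If status is meant, assumed control rates of 40%, 50%, 60% or 70% with a 15-point gain give 78.6%, 79.5%, 83.6% or 91.1% power at 167 per arm.

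**The case against.** The strongest reply is that little here is an error of inference. Four parts of it stand.

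- A reader might infer that the PEPPI t-tests miss the stated change endpoint. The documents do not support that. Under 1:1 randomisation the expected baseline means are equal, so the arm difference at follow-up has the same expectation as the arm difference in mean change. ANCOVA targets that same quantity. Only precision is lost, and the trial already meets its own power target for this aim.
- A reader might infer that the confidence test certainly ignores baseline. The text is ambiguous. If the dichotomy is improved versus not improved, the chi-squared test already uses baseline, and the 30% then differs from the planned outcome only in timing.
- A reader might extend the time-point conflict to both scales. Statistical methods {20a} gives no PEPPI time-points, so the conflict concerns Aim 3 confidence only.
- The 30% may be the only rate at hand. Sample size {14} says that the earlier study had no contact between its baseline and 4-month surveys, which would leave no on-treatment rate, although the retention section mentions intermediate contacts. The 4-month rate also fits the time-point in the analysis section.

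It can also be said that the two Aim 3 lists are incomplete versions of one plan, since Aim 3 covers effects during and after therapy. That is possible, but nothing in the protocol says so, and the lists still need reconciling. Nor does the reply rescue the baseline test: it is counted among the three planned arm comparisons and carries a power claim.

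Replacing the confidence dichotomy with a continuous score is a matter of judgement. It would abandon a cutoff that the plan describes as established, and would need a planning SD that the protocol does not give. It is not part of this point.

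**Conclusion.** The point holds for secondary Aims 3 and 4, as one of efficiency and consistency. The planned follow-up PEPPI t-tests are valid but leave collected information unused. The loss is 86% power against about 89% to 99%, resting wholly on an assumed correlation of 0.3 to 0.7. The baseline PEPPI test serves no purpose as a test of the app. The Aim 3 time-point conflict and the mix of status and improvement are in the text and need no assumed figure. The stated powers are correct given their own inputs. The primary job-retention analysis is untouched. The change should be made before the data are analysed.

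**What to change.** 1. Analyse follow-up PEPPI by ANCOVA, or one longitudinal model, with baseline score, recruitment site and language as covariates.
2. Drop the baseline PEPPI t-test and its power claim. Baseline scores can be described by arm without a test.
3. State the same Aim 3 confidence time-points in Sample size {14} and Statistical methods {20a}.
4. State whether the confidence dichotomy is status or improvement. If it is status, adjust for baseline confidence, for example by logistic regression.
5. Match the 30% planning rate to the chosen definition and time-point, or label it a proxy taken from the 4-month improvement rate.

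The cost is a revision of wording in two sections and of the secondary analysis models. No new data are needed, because baseline collection is already planned for both scales. If status is chosen, the Aim 3 power statement needs either a control rate for status, which the protocol does not now give, or the proxy label.

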### Recruitment {15}

Participants in all phases of the study (focus groups, interviews, and RCT) may be consented verbally over the phone or in person. All patient recruitment will be done by research staff who are consenting professionals with (when necessary) a volunteer affiliation with the collaborating study site. Bilingual research staff (Spanish-English) who are consenting professionals will recruit Spanish-speaking patients.

Data collected from patients who are ineligible will be maintained linked to an anonymized ID for the purposes of clinical trials reporting as per the Consolidated Standards of Reporting Trials (CONSORT) guidelines to optimize rigor and transparency in study results [49]. Patients who meet the criteria for inclusion will proceed with the informed consent process and, if they choose to participate, will be enrolled in the study.

A signed written informed consent form is not required for this study, based on the Code of Federal Regulations Title 45, Part 46, Subpart A, which states that an IRB may waive the requirement for an investigator to obtain a signed consent form for some or all subjects if it finds that the research presents no more than minimal risk of harm to subjects and involves no procedures for which written consent is normally required outside of the research context. Therefore, to help reduce subject burden and more efficiently use research resources, consents obtained for this study will be verbal. In all cases, participants will be given a written document (study information sheet) outlining their commitment and study procedures.

#### Usability testing participants

Usability testing participants may be recruited through oncology clinics at MSK, NYC Health & Hospitals/Lincoln Medical Center, and Montefiore Medical Center. Additionally, usability testing participants may also be recruited by the study team through the Memorial Sloan Kettering Cancer Center food pantries.

#### Community usability testing participants

In addition to the usability testing recruitment described above, our recruitment strategy for Spanish community usability testing participants will focus on the recruitment of a community sample of native Spanish speakers of different national backgrounds with special attention to occupational groups that are categorized as service and production type jobs (e.g., nanny, nail technicians/manicurists, and restaurant workers) as determined by our aggregation of the Bureau of Labor Statistics Standard Occupational Classification Policy Committee (SOCPC) [50]. The Immigrant Health and Cancer Disparities Service (IHCD) at Memorial Sloan Kettering Cancer Center, in which our research team is housed, has a longstanding relationship with the New York City Spanish-speaking community and community partners, to facilitate access to health services through its ongoing health fairs and education activities. Several of these organizations serve as regular meeting points for the Spanish-speaking community. We will utilize these existing community partnerships (e.g., the Mexican Consulate) to arrange a date and time for study personnel to approach and potentially enroll employees and/or community members on site. In addition, we will work with informal networks (e.g., groups of nannies, nail-salon workers) to advertise the study and set up a time to meet with interested participants. Whenever possible, usability testing will be done on site at MSK. We recognize that this location may be inconvenient for some participants, however, and if necessary, we will meet participants in appropriate public spaces (e.g., a café) that is near to the participant’s workplace.

Because medical information will not be collected about these participants, the study team sought and was granted a waiver to obtain informed consent from participants in the community-based usability testing phase of the study, based on federal regulations 45 CFR 46.116(d) and 21 CFR10.115(g) [2].

#### Focus group and interview participants

Participants in focus groups and interviews may include, in addition to patients treated at the clinical sites described above, patients identified through the community through the Integrated Cancer Care Access Network (ICCAN) or through breast cancer support organizations, such as LatinaSHARE, and patients who were previously enrolled in the BCW study [7]. Patients who meet the criteria for inclusion will be told about the study and, if they choose to participate, will be scheduled to attend a focus group or for an interview (in-person or over the phone) and sent a copy of the TEAMWork booklet by email and/or mail for their review prior to the focus group or interview. At the start of the focus group or interview, patients will be informed of the details of the protocol, including study overview and aims, study procedures, and the risks involved. After this open discussion, each participant will be consented individually by a consenting professional, in person or via phone.

#### RCT participants

The research team will contact the treating physician (surgeon or medical oncologist, depending on who has most recently seen the patient in clinic) to verify that it is acceptable for the team to approach each patient about the study. If at the time of the initial medical oncology consultation no definitive decision is made regarding whether a potential participant will undergo chemotherapy, the research staff will communicate with the oncology provider regarding the final recommendation and patient decision regarding systemic therapy.

Research staff will approach participants at a post-operative visit with the surgeon, at their initial consultation with the medical oncologist, or a patient meeting or workshop (after obtaining permission from the meeting or workshop leader) to describe the study. Staff may also call patients about the study, and leave a voicemail, when applicable.

Our target study population is often hard to reach due to changes in phone number, loss of phone service, limited phone service, treatment side effects, lack of fixed working schedules, and change in address. In prior research, our team has experienced difficulties contacting members of our target population for an initial approach. However, after multiple attempts, we generally have success reaching our population. As a result, potential participants may be contacted at least 3 times. If the team is unable to contact the patient by phone, the team may approach the patient in clinic and offer the opportunity to learn more about the study. If the patient declines to participate by phone, no further attempts will be made to contact the patient.

If an individual is interested in the study, the research staff will assess their eligibility by going through the inclusion and exclusion criteria and asking the individual a set of screening questions. Answers will be recorded in the screening log and/or on the participants’ eligibility checklist. Patients approached who do not meet the eligibility criteria or decline participation will be asked about their self-efficacy to request accommodations at work and their answers will be recorded.

After verifying eligibility and completing the informed consent process with those who wish to participate, study staff will give participants instructions on how to log onto the study website to complete an online survey at a later date, directions on how to complete the survey on an iPad in clinic, or administer the survey interview-style. At the time of enrollment, we also will ask participants to provide contact information for themselves as well as for two emergency contacts who we may reach in case we are unable to contact the participant for administration follow-up surveys. We will call each participant who has not completed a baseline survey within 1 week of enrollment to offer the opportunity to complete a survey interview-style (if participant prefers that to an online survey) or to remind the participant to log onto the website. If the participant prefers to complete a survey interview-style, the research staff will administer the survey and enter participant responses directly into the online survey in real time, on the participant’s behalf.

